## Abstract

**Background:**

Sexual dysfunction is prevalent in patients with type 2 diabetes mellitus, but remains one of the most frequently neglected complications in diabetes care. Both patients and care providers appear to have difficulty with discussing sexual problems in diabetes care. A sexual counselling model for care providers, such as the PLISSIT model, might be a useful tool to improve the discussion of sexual issues in patients with type 2 diabetes mellitus. PLISSIT stands for Permission, Limited Information, Specific Suggestions, and Intensive Therapy. Even though the use of the PLISSIT model has often been recommended in diabetes care, no evidence with regards to its effectiveness in patients with type 2 diabetes mellitus exists. This study describes the design of a cluster-randomised controlled trial evaluating the effectiveness of a PLISSIT-model intervention in men and women with type 2 diabetes mellitus in primary care.

**Methods/Design:**

Patients with type 2 diabetes mellitus, aged 40–75 years, who indicate to be dissatisfied about their sexual functioning and that they would like to talk about their sexual problem(s) with their general practitioner are recruited. All participants receive an information leaflet from the practice nurse. In the intervention group, each participant will also receive sexual counselling based on the PLISSIT model from their general practitioner. In the control group, usual care will be provided to those participants requesting an appointment with their general practitioner when the information leaflet was not deemed sufficient. Primary outcomes include sexual functioning, satisfaction about sexual function, and quality of life. Secondary outcomes are depressive symptoms, sexual distress, emotional well-being, and treatment satisfaction. Outcomes will be measured by means of self-report questionnaires at baseline, and after 3 and 12 months post-baseline. Treatment satisfaction will be assessed in telephone interviews.

**Discussion:**

This paper describes the design of a cluster-randomised controlled trial that will investigate the effectiveness of a PLISSIT-model intervention in patients with type 2 diabetes mellitus in primary care. Our study will add important and currently missing insight into the effectiveness of PLISSIT on important patient-reported outcomes of men and women with type 2 diabetes mellitus.

**Trial registration:**

Dutch Trial Registry NTR4807.

## Background

Sexual problems are highly prevalent among patients with type 2 diabetes mellitus (T2DM) [1, 2].

Although prevalence rates vary widely between studies, patients with T2DM are generally twice as often affected by sexual problems compared to persons without T2DM [3]. Men most frequently report erectile dysfunction (ED), with prevalence rates ranging from 36 to 84 % [4–9], followed by ejaculation disorders and hypoactive sexual desire disorder, 40 and 25 % respectively [7, 10]. In addition, ED is prevalent in newly diagnosed patients and is often comorbid with other sexual dysfunctions [11]. Among women, hypoactive sexual desire disorder and lubrication problems are common with prevalences of 46–82 % and 38–70 % respectively [12–15]. Women with T2DM also report arousal disorders (68 %), orgasmic disorders (38–84 %), and dyspareunia (43–46 %) [12–15].

Sexual dysfunction negatively affects the quality of life of patients with T2DM. Patients with diabetes rate their sex life as less satisfying than persons without diabetes [13, 14, 16]. Men with T2DM with ED report significantly worse emotional and psychological well-being, and more diabetes-related distress [17–19]. Even though less is known how sexual dysfunction affects the quality of life of women with T2DM, research in women with type 1 diabetes suggests a negative effect on quality of life as well [20]. Altogether, the high prevalence and negative effects of sexual dysfunction in patients with T2DM warrant clinical attention.

In the Netherlands, diabetes care is organised in primary care. Patients with T2DM generally have three-monthly control visits with the practice nurse and a yearly consultation with their general practitioner (GP). According to the Dutch Society of General Practitioners (NHG) diabetes treatment guideline, sexual issues should be addressed during this yearly appointment with the GP [21]. The GP should explicitly inquire whether the patient experiences sexual problems, including ED, loss of sexual desire, and decreased vaginal lubrication. In addition, the GP should discuss possible treatment options, such as medication adjustment [21]. Nevertheless these guidelines, sexual problems remain to be frequently neglected in diabetes care [22, 23].

Both GPs and patients experience difficulties when discussing sexual problems in clinical practice. Patients with T2DM feel embarrassed and would like the GP to initiate this discussion [23, 24], whilst GPs experience a lack of time, training, knowledge, and skills when doing so [25, 26]. Certain patient characteristics, such as gender, ethnicity, and sexual orientation, are mentioned by the GP as barriers for discussion as well [25, 26]. These difficulties impede the consultation of sexual problems in general practice. As negligence of sexual problems may only further decrease a patient’s quality of life [27], it is necessary to improve sexual counselling in diabetes care.

A sexual counselling model for care providers might be a useful tool in improving GP’s skills when discussing sexual issues with their patients. Over the past few decades, several models have been developed, such as ALARM [28], BETTER [29], and PLISSIT [30]. These models all take a somewhat different approach to sexual counselling, but have in common that little research has been conducted to study their effectiveness. The PLISSIT model, however, has shown promising features in women with sexual problems [31–33], stoma patients [34], and patients with gynaecological cancers [35, 36]. Moreover, it has been frequently recommended for health care professionals [37–39] and for diabetes care professionals specifically [3, 27, 40–42].

The PLISSIT model was developed by Annon as a framework for care providers to assist in the ordering and treatment of sexual problems [30]. PLISSIT is an acronym for the four stages of the model: Permission, Limited Information, Specific Suggestions, and Intensive Therapy. This four-step framework aides care providers with the discussion and treatment of sexual problems, whereby each step requires increasing skill and knowledge from the care professional [30]. Importantly, the use of the model is geared to the care provider’s competence, hence allowing them to refer patients for further treatment during each step.

Until now, the effectiveness of the PLISSIT model has not been examined in patients with T2DM. Considering the widespread recommendations, promising features, and beneficial findings in other patient groups, we will therefore conduct a cluster-randomised controlled trial (RCT) among patients with T2DM in Dutch primary care to examine the PLISSIT model’s effectiveness. Primary outcomes include patient-reported sexual function, satisfaction about sexual function, and quality of life. Secondary outcomes that will be considered are patient-reported depressive symptoms, emotional well-being, sexual distress, and treatment satisfaction.

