#### Primary outcome measures

Sexual function will be assessed with the 19-item Female Sexual Function Index (FSFI) for women [48], and the 15-item International Index of Erectile Function (IIEF) for men [49]. Both questionnaires are widely used and have been well-validated [50–52]. Satisfaction with sexual function will be measured on a 10-point Visual Analogue Scale (VAS) scale: ‘how satisfied are you with your sexual functioning on a scale from 0 to 10?’, where 0 indicates being very unsatisfied and 10 indicates being very satisfied. Quality of life will be assessed with the brief, reliable, and valid Short Form-12 item survey (SF-12) [53–55].

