### Sample size

We decided to settle for a power to detect an improvement of 25 % in sexual functioning, 10 % in the control group and 35 % in the intervention group. We calculated that 65 participants per group would be needed, assuming a two-sided test at an alpha of 0.05 and a power of (1 − beta) 0.90. Due to cluster randomisation at GP level, the sample size needed to be inflated based on the formula of the Design Effect: 1 + (n-1)∙ICC with n as the mean cluster size and ICC as the Intracluster Correlation Coefficient [64]. We estimate to recruit six eligible patients per practice (n=6). An ICC of 0.05 was chosen to account for the clustering of patients within practices [64, 65]. The Design Effect was calculated as 1.25. In addition, we accounted for a 20 % dropout. A total of 195 patients are needed. We will therefore aim to recruit 200 patients from 34 general practices.

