### Analyses

Since we have chosen a cluster-randomised design with repeated measurements, observations and patients within a certain cluster are more alike and thus correlate to each other. We will therefore use linear and logistic multilevel regression analyses to study the effects of our trial. Data will be analysed as intention-to-treat and differences in outcomes measures between the intervention and control group will be calculated with 95 % confidence intervals. Given that not every patient in the control group will have had an appointment with their GP, a sensitivity analysis will be conducted to compare patients who had an appointment with their GP in the intervention versus control group.

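### The sample size covers one test of sexual functioning, but three outcomes measured at two visits share primary status and none is ranked first

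*Protocol article*

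**What the plan says.** **Sample size.** The calculation concerns one outcome: "We decided to settle for a power to detect an improvement of 25 % in sexual functioning", specified as "10 % in the control group and 35 % in the intervention group". It is made "assuming a two-sided test at an alpha of 0.05" and "a power of (1 − beta) 0.90". It does not say at which visit these percentages are expected, and it gives no power for any other outcome.

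**Primary outcomes.** The Background says: "Primary outcomes include patient-reported sexual function, satisfaction about sexual function, and quality of life". The Abstract and the Discussion list the same three, and the section Primary outcome measures places all three under one heading without an order. In that section, "Sexual function will be assessed with the 19-item Female Sexual Function Index (FSFI) for women", and a different instrument is used for men.

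**Timing.** From the Abstract: "Outcomes will be measured by means of self-report questionnaires at baseline, and after 3 and 12 months post-baseline". No section names 3 or 12 months as the primary visit.

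**Analysis.** The Analyses section plans linear and logistic multilevel regression for clustered, repeated measurements. It says that "differences in outcomes measures between the intervention and control group will be calculated", with 95% confidence intervals. It does not say whether the effect is estimated at each visit or as one overall effect, nor which result or results would establish effectiveness.

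**The concern.** Which outcome and which visit are primary is a protocol-level choice, and it determines what the sample size means. Here the two parts do not match: three outcomes have equal primary status, while alpha and power are set for one of them.

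The trial is meant to show whether the PLISSIT intervention is effective. If any of the three outcomes can carry that conclusion, a claim presented at the 5% level has a larger error rate. If all three are needed, the trial may be less likely to succeed than the stated 0.90 suggests. On the text shown, the outcome and visit that support the conclusion are also not fixed in advance.

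**Working it through.** **1. Reproduce the plan's own figure.** Inputs from Sample size: p₁ = 0.10, p₂ = 0.35, difference d = 0.25, mean p̄ = 0.225, two-sided alpha 0.05 (z = 1.960), power 0.90 (z = 1.282).

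- n = [1.960·√(2·0.225·0.775) + 1.282·√(0.10·0.90 + 0.35·0.65)]² / 0.25² = 56.5, so 57 per group.
- With continuity correction: (n/4)·[1 + √(1 + 4/(n·d))]² = (56.5/4)·[1 + √1.283]² = 64.3, so **65 per group**, as stated.
- Design effect: 1 + (6 − 1)·0.05 = 1.25, and 130 × 1.25 = 162.5.
- Dropout: 162.5 × 1.20 = **195**, as stated.

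The stated total is thus exactly a one-test calculation.

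**2. If any one success suffices.** With k independent tests, each at two-sided 0.05, the chance of at least one false positive is 1 − 0.95^k.

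- Sexual functioning alone, tested at both visits (k = 2): 1 − 0.95² = 9.75%.
- Three outcomes, one test each (k = 3): 1 − 0.95³ = 14.3%.
- Three outcomes at two visits (k = 6): 1 − 0.95⁶ = 26.5%.

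The article gives no correlations, so they are assumed here. Simulation of correlated normal test statistics (1,000,000 draws) gives:

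| Tests | Assumed correlation | Chance of at least one false positive |
|---|---|---|
| 3 | 0.5 between outcomes | 12.6% |
| 3 | 0.7 between outcomes | 10.9% |
| 3 | 0.8 between outcomes | 9.8% |
| 6 | 0.3 between all six | 24.2% |
| 6 | 0.3 between outcomes, 0.6 between visits | 22.9% |
| 6 | 0.5 between outcomes, 0.7 between visits | 20.3% |
| 6 | 0.7 between outcomes, 0.8 between visits | 16.5% |
| 6 | 0.8 between outcomes, 0.9 between visits | 13.5% |

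For correlations between outcomes up to 0.7, three tests give about 11–14%. Six correlated tests give about 16–24% over the 0.3 to 0.7 rows. Still stronger correlation lowers both, but even the most favourable row is close to twice 5%.

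**3. If all three must succeed.** No adjustment of alpha is needed, but joint power falls. Assume, for illustration, that each outcome had 0.90 power at one visit. Joint power would be 0.9³ = 0.729 if the outcomes were independent, and between 0.729 and 0.90 if they were positively correlated. The article gives no power for satisfaction or quality of life, so the true value cannot be calculated.

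**4. If alpha were split equally over three outcomes.** At 0.05/3 = 0.0167, the same formula with continuity correction needs 81 per group. The plan's own inflation steps then give 162 × 1.25 × 1.20 = 243, against 195 stated and 200 targeted. At 65 per group, power for 10% against 35% (without continuity correction) falls from 93.6% to 85.7%.

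**The case against.** The strongest reply is that this is a condensed article with one short analysis paragraph. Testing order, alpha split and success rules are commonly placed in a statistical analysis plan, which is not shown. That stands: a missing adjustment is not the point, and it cannot be said that the sponsor has no rule. What remains is on the page: three unranked primary outcomes, no primary visit, and a sample size for one of the outcomes.

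A reader might go further and infer that the false-positive rate is 21–27%. The documents do not support that as a fact. It requires separate tests at both visits, that any single success counts, and only modest correlations. The article states none of these. The Analyses section describes models for repeated measurements, which could give one overall effect per outcome and hence three tests. Alpha 0.05 appears only in the sample size calculation; the analysis plan speaks of confidence intervals and not of a significance rule.

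A reader might also count sexual function as two tests because men and women complete different instruments. The sample size points the other way: it compares one pooled proportion per arm, with no split by sex.

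Finally, a fixed testing order is only one valid remedy, and nothing in the article dictates the order of the other two outcomes. That also stands.

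**Conclusion.** The point holds as a mismatch between the primary outcomes and the sample size. The 65 per group and 195 in total are right for one test of sexual functioning and do not cover three outcomes of equal standing.

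- If any one outcome can support the claim, the error rate is above 5%: roughly 11–14% with one test per outcome, and at most 26.5% with six tests at 0.05.
- If all three must succeed, the 0.90 power does not apply to the joint claim.
- If sexual functioning alone was meant to decide, the calculation fits, but the outcome list does not say so and the visit is still open.

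The size of the inflation depends on the number of tests, the success rule and the correlations, all of which are assumed here. This is a correctable flaw in how the primary claim is fixed. It does not invalidate the sample size arithmetic.

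**What to change.** In Primary outcome measures and Sample size, name sexual functioning as the single primary outcome at one pre-stated visit: the visit at which 10% against 35% is expected. Use the same designation in the Abstract, Background and Discussion.

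Make satisfaction with sexual function and quality of life key secondary outcomes at that visit. Test them in a pre-stated fixed order, each at 0.05 only if the previous test succeeds, or under another stated familywise control. Report the other visit as supportive. The choice of visit and the order of the two key secondary outcomes belong to the sponsor, and both should be settled before outcome data are compared by arm.

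**Cost.** The primary test keeps the full 0.05 and the sample size is unchanged. Satisfaction and quality of life can be claimed only if sexual functioning succeeds. The sponsor must commit to a visit, which is a substantive assumption about when the powered effect occurs. A single outcome across the male and female instruments also needs one definition of improvement that serves both; if the full protocol already has one, a reference to it is enough.

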## Methods

### Design and setting

This study is a cluster RCT, registered at the Dutch Trial Registry (NTR4807). The study protocol was peer-reviewed by the Dutch Diabetes Research Foundation. The study was approved by the Medical Ethics Committee of the VU University Medical Centre in Amsterdam, The Netherlands.

The study will be conducted in primary care practices in the western part of the Netherlands: the West-Friesland region, the Zaanstreek-Waterland region, and Amsterdam area. Both urban and rurally located general practices will be included. Randomisation takes place at the level of general practice. Eligible patients will either be included in the intervention or control group: structured sexual counselling based on the PLISSIT model versus unstructured sexual counselling (usual care).

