**Fig. 2 Fig2:**
[figure not shown]
The modified Brief Sexual Symptom Checklist for Women (BSSC-W)

Based on the results of the screener, patients are eligible for study participation if they report 1) to be sexually dissatisfied, and 2) that they would like to talk about their sexual problem with the GP. The practice nurse will explain that a scientific study program is tested in this practice, and that the particular patient is eligible for participation. Participation implies that the patient will need to fill out three questionnaires in the coming 12 months.

After handing in the baseline questionnaire, the patient receives an information leaflet from the practice nurse on Diabetes and Sexuality. In the intervention group, the practice nurse will subsequently make an appointment with the GP for each patient to talk about sexual problems. Practice nurses in the control group do not automatically make an appointment with the GP for every patient. Instead, the practice nurse will ask whether the information leaflet was of sufficient help or whether the patient would like to have an appointment with his/her GP nevertheless.

The practice nurse will fill notify the researchers if a patient consented to participate. A non-response form is filled out for those patients who do not agree to fill out the screener and/or do not want to participate in our study. The form includes the patient’s gender, year of birth, and ability to speak/read Dutch.

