### Control group

GPs in the control group provide care as usual [21]. At present, apart from the NHG guideline about ED [47], no NHG guideline regarding male or female sexual dysfunction exists. The GP will provide usual care conform the NHG guideline on depressive symptoms when deemed necessary [46], as previously described in the intervention strategy paragraph.

In order to establish equal referral options for both study arms, GPs in control practices will receive the same overview of specialists to whom they may refer their patients for further treatment. By providing both groups with this map we can correct for the effect a referral may have on our outcomes.

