A limitation to our study is that the external validity has to some extent been compromised by the increased internal validity. First, by specifically instructing the practice nurses in both groups to identify sexual problems, we raise more attention to the topic than usual care would normally comprise. Moreover, it is expected that GPs in the control group will also tend to pay more attention to sexual problems, although it is assumed that this effect will fade over time as the trial progresses. Second, the practice nurse implicitly performs the first step of the PLISSIT model (Permission) by handing out the screener which asks ‘Would you like to talk about it with your GP?’. This is, however, most similar to usual care where the practice nurse will screen for health problems before sending the patients to the GP.

In conclusion, the present study will evaluate the effectiveness of a PLISSIT model intervention in patients with T2DM in primary care. These findings will contribute to the field of T2DM and sexual dysfunction.

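### The contrast is stated as structured versus unstructured counselling, but the arms also differ in arranged GP access, so the result belongs to the package and not to PLISSIT alone

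*Protocol article*

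**What the plan says.** The Design and setting section defines the two arms as "structured sexual counselling based on the PLISSIT model versus unstructured sexual counselling (usual care").

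The Recruitment section sets out what happens to patients. In both arms, eligibility requires that patients report sexual dissatisfaction and "that they would like to talk about their sexual problem with the GP". All receive the leaflet. After that the arms diverge:

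- Intervention: "the practice nurse will subsequently make an appointment with the GP for each patient to talk about sexual problems".
- Control: "Practice nurses in the control group do not automatically make an appointment with the GP for every patient"; the nurse asks whether the leaflet was enough or an appointment is still wanted.

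The Abstract agrees with Recruitment: in the control arm "usual care will be provided to those participants requesting an appointment with their general practitioner when the information leaflet was not deemed sufficient".

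Usual care is described in three places. The Background says that under the Dutch diabetes guideline "sexual issues should be addressed during this yearly appointment with the GP", and adds that in practice the topic is often neglected. The Control group section says that control GPs give care as usual and cites the same guideline. The Discussion defends the screener as "most similar to usual care where the practice nurse will screen for health problems before sending the patients to the GP".

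The Analyses section plans an intention-to-treat analysis. It acknowledges that not every control patient will have seen the GP and adds a sensitivity analysis comparing those who did, by arm.

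**The concern.** The stated contrast varies one thing, the manner of counselling. The procedures vary two: whether a consultation is arranged, and whether the GP is trained in PLISSIT. A control patient content with the leaflet receives no GP counselling under the trial procedure, so for that patient there is no unstructured counselling to compare with.

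Access is a plausible active ingredient here. The Background says that patients are embarrassed and would like the GP to open the subject. Arranging the appointment removes that barrier in one arm; in the other, the patient has to confirm the wish a second time.

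The end of the Background gives the aim as the effectiveness of the PLISSIT model, and the Discussion speaks of the effectiveness of PLISSIT. A positive result reported in those terms would credit the counselling model with an effect that might come partly or wholly from the arranged visit. The limitations paragraph treats the control procedures as a cost to external validity only and does not mention unequal access.

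**Working it through.** **Step 1. The arms side by side** (Recruitment, Training of practice nurses, Training of GPs in the intervention group, Control group).

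| Element | Intervention | Control |
|---|---|---|
| Wants to talk to the GP | required | required |
| Nurse training, screener, leaflet | yes | yes |
| Overview of referral options | yes | yes |
| GP appointment | made for every patient | only if wanted after the leaflet |
| GP trained in PLISSIT | yes | no |

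Two rows differ. The stated contrast names only the last.

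**Step 2. The planning figures.** The Sample size section gives 10% versus 35% improved, two-sided alpha 0.05, power 0.90, and 65 per group. The formula for two proportions gives 57 without continuity correction and 65 with it. The design effect is 1 + (6 − 1) × 0.05 = 1.25. Then 2 × 65 × 1.25 = 162.5, and 162.5 × 1.20 = 195. The figures reproduce; they are used below only as a scale.

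**Step 3. What the intention-to-treat difference contains.** Let c be the share of controls who see the GP, V the improvement rate with an ordinary GP visit, and L the rate with the leaflet alone. Assume that all intervention patients attend and 35% improve, and that V and L do not depend on who asks for a visit. Then

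D = 0.35 − [cV + (1 − c)L] = (0.35 − V) + (1 − c)(V − L).

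The first term is due to PLISSIT, the second to access. The Process analysis section records GP conversations, so c will be known. Even so, D does not fix the split. With c = 0.5:

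- V = 0.35, L = 0.10: control rate 22.5%, D = 12.5 points, all from access.
- V = L = 0.225: control rate 22.5%, D = 12.5 points, all from PLISSIT.

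The uptake and the result are the same, and the conclusions about PLISSIT are opposite.

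**Step 4. How large the access term could be.** Set V = 0.35, so that PLISSIT adds nothing and D = (1 − c)(0.35 − L). The article gives neither c nor L, so both are assumed. D in percentage points:

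| c | L = 0 | L = 0.05 | L = 0.10 |
|---|---|---|---|
| 0 | 35 | 30 | 25 |
| 0.25 | 26.25 | 22.5 | 18.75 |
| 0.50 | 17.5 | 15 | 12.5 |
| 0.75 | 8.75 | 7.5 | 6.25 |

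The planned 25 points arise at c = (0.10 − L)/(0.35 − L): 0.286 for L = 0, 0.167 for L = 0.05, and 0 for L = 0.10.

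With 200 recruited, the effective size is 200 × 0.8 / 1.25 / 2 = 64 per arm. For L = 0.10 and no PLISSIT effect, the chance of a significant result favouring the intervention (normal approximation, no continuity correction) is about 0.93, 0.69, 0.34 and 0.11 for c = 0, 0.25, 0.50 and 0.75.

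**Step 5. The attender comparison.** Its intervention side is nearly everyone, because everyone is booked. Its control side is the subset who still wanted an appointment after reading the leaflet. Membership is settled after randomisation and by a different rule in each arm, so the groups need not be comparable. The direction of the resulting bias cannot be told from the article.

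**The case against.** The strongest defence is that this is a legitimate pragmatic comparison of two strategies. Practices are randomised, so the intention-to-treat contrast is a valid estimate of what it compares. The Abstract and Recruitment sections describe both arms accurately, the object is often called a PLISSIT-model intervention, and the Analyses section admits that not all controls will see the GP. All of this stands. A reader might infer that the trial can say nothing useful about PLISSIT; that goes too far, since it can support a conclusion about the package.

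It can also be argued that provider initiation belongs to the model, since its Permission step is an invitation to talk. This helps only in part. The Intervention section places that step inside the GP consultation, and the Discussion says that the nurse already performs it implicitly through the screener, which both arms use.

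A reader might further infer that the leaflet step pushes control access below usual care and so tilts the trial towards PLISSIT. The article does not support that. The Background says the topic is often neglected despite the guideline, the Discussion says that both arms give it more attention than usual care would, and the control nurse actively offers an appointment. The Discussion sentence about sending patients to the GP defends the screener and refers to health problems in general.

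Nor do the leaflet, nurse training and referral overview confound the comparison. Both arms receive them; they qualify the usual-care label and may narrow the contrast.

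Finally, setting an untrained GP's results equal to those of a PLISSIT-trained one is an extreme assumption, given that the Background reports GPs lacking training and skills. The figures show what is possible, not what is likely.

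**Conclusion.** The point holds in a limited form. The contrast in Design and setting is not the one that the procedures create. The primary comparison estimates the joint effect of arranged GP access and PLISSIT counselling, and nothing in the plan separates the two on a randomised basis.

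The size of the access component is unknown. It could be nil, if an ordinary visit does no better than the leaflet. It could be the whole difference, if an ordinary visit does as well as PLISSIT. The control uptake, the leaflet-only rate and the effect of an ordinary visit behind the illustration are all assumptions. The validity of the randomised comparison of packages is not in question, and no claim is made that control access is below actual usual care.

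**What to change.** 1. At the end of the Background, in Design and setting, and in the Discussion, restate the comparison as leaflet plus a pre-arranged consultation with a PLISSIT-trained GP, versus leaflet with a GP consultation on request (modified usual care).
2. State that conclusions concern this package and that an effect cannot be attributed to PLISSIT counselling alone.
3. In Analyses, label the comparison of GP attenders as non-randomised and supportive only.
4. Reconcile the accounts of usual care in Background, Control group and Discussion with the control procedure in Recruitment, and add unequal GP access to the limitations.

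This changes only text, with no effect on sample size, visits or data collection. The price is a narrower claim. Using the same booking procedure in both arms would isolate GP training, but it would change the trial question and need an amendment; that is a design trade-off for the sponsor and is not needed to correct this point.
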